#### Primary outcome analyses

The primary hypothesis is that 12 weeks of yoga will be more effective than education for improving pain and function. For both outcomes, we will determine if yoga is superior to education based on a longitudinal model incorporating all measurements across the study period, including baseline, week 6, week 12, and week 24. The primary hypothesis will be tested using a contrast of the change from baseline to week 12 comparing the two groups within this model. To account for correlation among repeated measures for the same individual, we will assume an unstructured covariance for the initial model. A simpler model may be used for the covariance if appropriate. No missing data will be replaced in these analyses, and all available data can be included. The analysis is considered to be unbiased under a missing-at-random assumption. It is possible that any missing data may be non-ignorably missing rather than missing-at-random. We will perform sensitivity analyses to determine if the results are robust to the missing data mechanism. Note that we require statistical significance for both outcomes rather than either outcome to address the issue of multiple testing. We will report mean differences between groups with standard errors, 95 % confidence intervals, and *p* values. If the analysis of the success of randomization finds any imbalance between groups, the above model will be adjusted for these factors.

Per-protocol analysis will also be conducted similarly. Adherence to the yoga protocol will be defined as attending at least 9 of the 12 yoga classes. For education, adherence will be defined as reading at least three-fourths of the book by self-report.

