### Sample size

We assume a two-sided α = 0.05. This is justifiable because, although there are two primary outcomes, they are not independent. We use 2.5 as the standard deviation for the mean pain change score between baseline and 12 weeks, which is what was found in previous yoga-cLBP studies [37]. We also assume a 20 % dropout rate based on previous studies [37]. Thus, a sample size of 120 participants randomized to yoga vs. education provides 97 % power to demonstrate a minimal clinically significant difference in pain score of 2.0 [74]. For the RMDQ change score, if we assume a standard deviation of 5.0 [35, 37] and a minimal clinically significant difference of 3.0 [75], we have 82 % power to show a statistically significant difference between the two groups. Finally, if we assume that 50 % of the study participants with cLBP have a baseline PTSD CheckList – Civilian Version (PCL-C) score ≥30 and a standard deviation for the PCL-C change score of 12 [76, 77], there is 80 % power to demonstrate a minimal clinically meaningful difference in PCL-C of 10 points.

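### The primary contrast of change from baseline is described without a common baseline mean; it is valid, but adding that constraint is a free precision gain, mainly for the RMDQ

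*Protocol article*

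**What the plan says.** The section Primary outcome analyses sets the model, the test and the covariance. Superiority for each co-primary outcome is judged "based on a longitudinal model incorporating all measurements across the study period, including baseline, week 6, week 12, and week 24". Baseline is therefore a response, not a covariate. For the covariance, "we will assume an unstructured covariance for the initial model". The test itself is given as: "The primary hypothesis will be tested using a contrast of the change from baseline to week 12 comparing the two groups within this model".

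Adjustment is conditional. The Data analysis section compares the arms on baseline characteristics at α = 0.1, and the primary section adds: "If the analysis of the success of randomization finds any imbalance between groups, the above model will be adjusted for these factors". Nothing says that the arms share a baseline mean in the model, and nothing says that each arm has its own.

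The Sample size section works on the change-score scale. For pain, "We use 2.5 as the standard deviation for the mean pain change score between baseline and 12 weeks"; for function, "For the RMDQ change score, if we assume a standard deviation of 5.0". The Randomization section places the baseline survey before allocation. The primary section requires significance on both outcomes. The analyses of the SF-12 scores and of PCL-C refer back to the primary method.

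**The concern.** When baseline is a response and each arm has its own baseline mean, an unstructured model has no reason to borrow anything from the baseline comparison. Its week-12 contrast is then the difference between arms in mean change. Because baseline is measured before allocation, any baseline difference between the arms is pure chance. A model that knows this uses baseline only as far as it predicts week 12. A change score subtracts the full baseline difference whatever the correlation, and so adds noise.

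What is at stake is precision. The RMDQ has the lower stated power of the two co-primary outcomes (82 % against 97 % for pain). Since both must be significant, the RMDQ limits the chance of a positive trial. The same choice carries over to SF-12 and PCL-C.

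**Working it through.** **Inputs from the protocol article.** N = 120, allocation 1:1, 20 % dropout, hence 120 × 0.8 / 2 = 48 per arm; two-sided α = 0.05; pain difference 2.0 with SD of change 2.5; RMDQ difference 3.0 with SD of change 5.0.

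**Inputs not in the article, assumed.** ρ, the baseline–week 12 correlation: 0.3, 0.5, 0.7. k, the SD at baseline divided by the SD at week 12: 1, then 0.6 to 1.2.

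**1. The plan's own figures.** Two-sample t test, noncentrality = difference / (SD × √(2/48)).
- Pain: 2.0 / (2.5 × 0.2041) = 3.92, power 97.3 % (stated: 97 %).
- RMDQ: 3.0 / (5.0 × 0.2041) = 2.94, power 82.9 % (stated: 82 %).

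Both reproduce. The stated power is the power of a change-score comparison.

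**2. What the contrast is.** Take complete data, a common SD σ at every visit and n per arm. The variance of the week-12 contrast was computed by generalized least squares for the four-visit model, in units of σ²/n:

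| ρ | Free baseline means | Change score, 4(1−ρ) | Common baseline mean | 2(1−ρ²) | Reduction |
|---|---|---|---|---|---|
| 0.3 | 2.80 | 2.80 | 1.82 | 1.82 | 35 % |
| 0.5 | 2.00 | 2.00 | 1.50 | 1.50 | 25 % |
| 0.7 | 1.20 | 1.20 | 1.02 | 1.02 | 15 % |

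With free baseline means the contrast is exactly the change-score comparison. The reduction is 1 − (1+ρ)/2 = (1−ρ)/2.

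**3. Unequal SDs.** Relative to the week-12 variance, the change score has variance 1 + k² − 2kρ and the common-baseline estimator 1 − ρ². The difference is (k − ρ)², so

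reduction = (k − ρ)² / (1 + k² − 2kρ).

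This is never negative and is zero when k = ρ.

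| k | ρ = 0.3 | ρ = 0.5 | ρ = 0.7 |
|---|---|---|---|
| 0.6 | 9 % | 1 % | 2 % |
| 0.7 | 15 % | 5 % | 0 % |
| 0.8 | 22 % | 11 % | 2 % |
| 1.0 | 35 % | 25 % | 15 % |
| 1.2 | 47 % | 40 % | 33 % |

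**4. RMDQ power, 48 per arm, t test.** The SD of change, 5.0, is multiplied by √(1 − reduction).
- k = 1: from 82.9 % to 95.0, 91.9 and 88.4 % at ρ = 0.3, 0.5 and 0.7.
- k = 0.8: to 90.7, 86.8 and 83.6 %.

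Pain with k = 1 goes from 97.3 % to 99.8, 99.4 and 98.8 %.

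**5. Dropout.** Assume 80 % complete, 10 % lost after week 6 and 10 % lost after baseline, equal SDs, and the same correlation between all visits. The variances are 3.24 against 2.26, 2.35 against 1.85, and 1.43 against 1.25, so the reductions are 30, 21 and 13 %. The mixed model already recovers some information from dropouts. With 60 randomized per arm and a normal approximation, the RMDQ variance is (2 × 25/60) × (GLS variance) / [4(1−ρ)]. Power goes from 86, 86 and 85 % with free baselines to 96, 93 and 90 % with a common baseline.

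**6. Does the conditional adjustment rule supply the gain?** A baseline factor entered as a main effect shifts a person's four expected values by the same amount. With complete data it therefore drops out of a within-person change and leaves the contrast as it was. And if the imbalanced factor is the baseline pain or RMDQ score itself, the same measurement would be both a response and a covariate.

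**The case against.** The strongest reply is that the constraint is missing only in the sense that it is not mentioned. A constrained longitudinal model also has baseline as a response, and its week-12 treatment term is also a between-arm contrast of change. The wording fits both models, and a statistical analysis plan that is not shown may settle the matter. This stands as far as it goes: the text does not rule out a constrained model. But the constraint is not the default, and screening the arms for baseline differences with adjustment only on a finding points away from it. The article does fix the responses, contrast, covariance and adjustment rule, so the mean structure is worth one more sentence.

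Second, a reader might infer that 15–35 % of the information is lost on every outcome. The documents do not support that. The range needs ρ between 0.3 and 0.7 and equal SDs, and neither is given. Pain has an entry threshold of 4 on the 0–10 scale, and the PCL-C subset is selected on a baseline score of 30 or more. Both rules probably make the baseline SD smaller than the week-12 SD, and the reduction can then be close to zero. No such threshold applies to the RMDQ, but equal SDs are an assumption there too.

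Third, a reader might infer that the planned test is biased or the trial underpowered. Neither follows. The change contrast is unbiased over randomization. It misjudges the effect only conditionally on a chance baseline difference, and the imbalance screen is at least meant to react to the larger ones. The sample size uses change-score SDs, so the stated 97 % and 82 % already include the inefficiency.

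Finally, keeping every participant with any measurement is no advantage of the constrained model, because the planned model already does so.

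**Conclusion.** The point holds as an efficiency matter, not as an error. The analysis as described is valid and consistent with the sample size calculation. Read plainly, it leaves unused the equality of baseline means that randomization guarantees. A common-baseline model is never less precise, and the imbalance rule does not replace it.

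The benefit cannot be fixed from the article. For the RMDQ with equal SDs and ρ from 0.3 to 0.7, variance falls by 35 to 15 % (30 to 13 % under the assumed dropout), and power at 48 per arm goes from about 83 % to between 95 and 88 %. If the baseline SD is 0.8 of the week-12 SD, power reaches only about 91 to 84 %; if it is larger than the week-12 SD, the gain exceeds the equal-SD figures. Pain has little to gain, since it already stands at 97 %. For the PCL-C ≥30 subset the gain may be small or absent.

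**What to change.** Keep the four-visit model with unstructured covariance and add one sentence on the mean structure: the two arms share a single baseline mean. The fixed effects are then time and treatment by post-baseline time, with no treatment effect at baseline. Test the treatment term at week 12 for pain and for the RMDQ, and use the same model for SF-12 and PCL-C, including the PCL-C ≥30 subset, which is itself defined before allocation. If the constraint is already intended, say so.

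The cost is wording only: no extra participants, visits or data. The published sample size can stand, since its power figures are then conservative for this aspect. The article reports that recruitment is still under way, so the change can be fixed before outcomes are analysed.

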### Randomization

The baseline survey is typically completed within 45 days after eligibility screening. If the period since screening exceeds 45 days, eligibility is re-assessed and verified prior to the baseline survey. After completion of the baseline survey, the participant is randomized in a 1:1 ratio to yoga or education using StudyTRAX™ (Macon, GA), a HIPAA-compliant study management software platform. Permuted block randomization with varying block sizes of two or four is used. Stratification is done on three dichotomous variables to assure similar distribution between the two groups:Age (≤45, >45 years). Back pain in older Veterans may be structurally different. Furthermore, age may be a confounding variable to the response to yoga.PCL-C score (<30, ≥30). These cut-offs will help assure equivalent numbers of Veterans with PTSS in both treatment arms in order to compare the effectiveness of the interventions for reducing comorbid PTSS. PTSS may also be an effect modifier for yoga and cLBP.Partnered (yes/no). A partnered Veteran is defined as one who reports having a cohabitating or long-term committed partner/spouse. This helps assure adequate numbers of partnered Veterans in the yoga group available for qualitative interviews.

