Yoga classes contain no more than eight to ten Veterans and two yoga teachers to assure a low Veteran-to-instructor ratio (no more than five Veterans to one teacher). This arrangement maximizes effectiveness and safety, and allows flexibility in yoga teacher scheduling based on the study’s needs. Veterans are asked to attend one 75-minute class per week and receive reminder phone calls the day before each scheduled class. Attendance is taken by research staff. We provide $10 travel compensation for each yoga session. Mats and props are provided. Each class includes a yoga breathing exercise (*pranayama*), discussion of yoga philosophical principles, yoga postures (*asanas*), and a relaxation exercise (*svasana*). Veterans are frequently advised to proceed carefully and slowly. The difficulty of postures increases throughout the 12 weeks (Table 2). The 12-week intervention period is divided into four 3-week segments, titled Opening to Something New, Listening to Your Back, Engaging Your Power, and Bringing it Home. Posture variations, modifications, and various aids (e.g., block, chair, strap, wall) are built into the protocol to accommodate a range of abilities. Yoga participants are encouraged to practice at home for 30 minutes on days when they do not have class. To help Veterans practice at home, they receive a guidebook describing and depicting the protocol (see Additional file 1), yoga mat, strap, two blocks, and home practice instructional videos (see Additional file 2-5). Home practice videos portray Veterans in an introductory video describing the value of yoga practice in their own lives, two 30-minute videos that follow the same structure as group yoga classes, and one 20-minute extended breathing and relaxation video. Veterans are given a link to view the home practice videos online or, if requested, they receive a take-home DVD.

**Table 2 Tab2:** Twelve-week standardized hatha yoga protocol

Yoga posture (*asana)* or class component	Classes incorporating component by segment			
	Segment 1	Segment 2	Segment 3	Segment 4
	Weeks 1–3	Weeks 4–6	Weeks 7–9	Weeks 10–12
	Opening to Something New	Listening to Your Back	Engaging Your Power	Bringing it Home
Breathing exercise	✓	✓	✓	✓
Knees to chest pose^*^	✓	✓	✓	✓
Knees together twist pose	✓	✓	✓	✓
Pelvic tilt pose^*^	✓			
Big toe pose^*^		✓	✓	✓
Cat and cow pose*	✓		✓	
Wheel pose^*^	✓		✓	
Chair pose^*^	✓	✓	✓	
Shoulder openers^*^	✓	✓	✓	✓
Crescent moon pose^*^	✓	✓		✓
Mountain pose^*^	✓	✓	✓	✓

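### Yoga is delivered in shared classes and education individually, but the primary model and the power statement treat Veterans as independent; if class outcomes correlate, intervals are too narrow and RMDQ power is overstated

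*Protocol article*

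**What the plan says.** The Hatha yoga section describes weekly group teaching over 12 weeks: "Yoga classes contain no more than eight to ten Veterans and two yoga teachers to assure a low Veteran-to-instructor ratio". The Education section describes a book handed to each person, with mailed newsletters and check-in calls. Allocation is individual: "the participant is randomized in a 1:1 ratio to yoga or education" (Randomization).

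Primary outcome analyses specifies a longitudinal model over baseline and weeks 6, 12 and 24, with a contrast of the change to week 12. On dependence between observations it says: "To account for correlation among repeated measures for the same individual, we will assume an unstructured covariance for the initial model". The only flexibility it adds is a simpler covariance structure. Success requires significance on both pain and RMDQ. PCL-C is to be analysed by similar methods (Psychological and exploratory analyses).

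The Sample size section states "We assume a two-sided α = 0.05", "We also assume a 20 % dropout rate based on previous studies" and "We use 2.5 as the standard deviation for the mean pain change score between baseline and 12 weeks", and concludes that "a sample size of 120 participants randomized to yoga vs. education provides 97 % power" for a 2.0-point pain difference. It gives 82 % for RMDQ and 80 % for PCL-C. It mentions no ICC, design effect or number of classes.

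**The concern.** Veterans in one yoga class share two teachers, the same peers and the same sessions for 12 weeks. Education Veterans share nothing comparable. Any class or teacher influence makes yoga outcomes alike within a class, in one arm only. A model that allows for correlation only within a person then counts the yoga Veterans as more independent information than they are.

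Two things are at stake. The article promises a standard error, 95 % confidence interval and p value for each co-primary outcome, and these would be too favourable whichever way the estimate points. The quoted power would also exceed what the design delivers. RMDQ matters most: both outcomes must be significant, and RMDQ starts at only 82 %, so its power caps the power of the primary claim.

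**Working it through.** **Inputs from the Sample size section.** Two-sided α = 0.05; 120 randomized 1:1; 20 % dropout, so 60 × 0.8 = 48 completers per arm. Pain: difference 2.0, SD 2.5. RMDQ: difference 3.0, SD 5.0. PCL-C: difference 10, SD 12, in half the sample, so 24 per arm.

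**Reproducing the stated power.** SE = SD × √(2/n), with noncentral t power on 2n − 2 degrees of freedom.
- Pain: SE = 2.5 × √(2/48) = 0.510; 2.0/0.510 = 3.92; power 97.2 % (stated 97 %).
- RMDQ: SE = 5 × √(2/48) = 1.021; 3.0/1.021 = 2.94; power 82.9 % (stated 82 %).
- PCL-C: SE = 12 × √(2/24) = 3.464; 10/3.464 = 2.89; power 80.7 % (stated 80 %).

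With 60 per arm (30 for PCL-C) the results are 99.2, 90.3 and 88.8 %, which do not match. The stated figures therefore allow for dropout but not for clustering.

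**Assumed inputs.** The number of classes is not stated. Sixty yoga Veterans in classes of 10 make 6 classes; in classes of 8 they make 60/8 = 7.5, taken as 8. With 48 completers, the mean number per class is m = 48/6 = 8 or 48/8 = 6. The ICC is not given and is taken as 0.01 to 0.10. Total SD is held at the stated value. For PCL-C, half of each class is assumed to be in the subset (m = 4 or 3).

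**Formulas.** Yoga-arm design effect D = 1 + (m − 1) × ICC. SE = SD × √((D + 1)/n), because the education arm is not inflated. The ratio of this SE to the planned model's SE is r = √((D + 1)/2). Type I error of the planned test on one outcome is approximately 2 × P(T > t₀.₉₇₅/r), with 94 degrees of freedom.

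**One case in full.** RMDQ, 6 classes, ICC 0.05: D = 1 + 7 × 0.05 = 1.35; SE = 5 × √(2.35/48) = 1.106; 3.0/1.106 = 2.71; power 76.5 %; r = √(2.35/2) = 1.084; type I error 7.0 %.

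**Results (range over 8 and 6 classes).**

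| | ICC 0.01 | ICC 0.02 | ICC 0.05 | ICC 0.10 |
|---|---|---|---|---|
| Yoga-arm design effect | 1.05–1.07 | 1.10–1.14 | 1.25–1.35 | 1.50–1.70 |
| True SE / model SE | 1.01–1.02 | 1.02–1.03 | 1.06–1.08 | 1.12–1.16 |
| RMDQ power, % | 82 | 80–81 | 77–78 | 71–74 |
| Pain power, % | 97 | 96–97 | 95–96 | 92–93 |
| PCL-C power, % | 80 | 80 | 78–79 | 75–77 |
| Type I error per outcome, % | 5.3–5.4 | 5.6–5.8 | 6.4–7.0 | 7.9–9.1 |

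A simulation of the ordinary t test (40,000 replicates, 48 per arm) gave 5.5–5.6, 6.6–7.0 and 8.1–9.2 % type I error at ICC 0.02, 0.05 and 0.10.

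**Class-level degrees of freedom.** A valid test must estimate yoga-arm variance from 6 to 8 classes. With V₁ = SD² × D/48 and V₂ = SD²/48, the approximate degrees of freedom for a test on class means with k classes are (V₁ + V₂)² / (V₁²/(k − 1) + V₂²/47). For RMDQ with 6 classes at ICC 0.05, V₁ = 0.703 and V₂ = 0.521, which gives 14.3 degrees of freedom and 71 % power; with 8 classes it is 75 %. The same test at ICC 0 gives only 79–81 %, so part of that fall is the price of the test and not of clustering.

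**The case against.** The strongest reply is that this is a condensed article, that its analysis plan is not shown, and that a class effect is ordinary content for such a plan. The quoted sentence concerns within-person covariance and does not exclude a class term. This does not dispose of the point. The article chose to write out both the correlation structure and the power inputs, and both are those of independent Veterans.

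Other parts of the reply stand:
- A reader might infer that the standard errors are shown to be too small. They are not: that needs an ICC above zero, and the documents give none. At ICC 0.01 the stated powers hold within rounding, and at 0.02 the loss is a point or two.
- A reader might infer that the primary claim carries an 8–9 % false-positive rate. That figure is per outcome, at ICC 0.10. If yoga affects neither outcome, both tests are significant in only about 1–2 % of simulated trials (assumed between-outcome correlation 0.5, ICC 0.02–0.10). The inflation reaches the joint claim mainly when yoga truly affects one outcome only; the joint rate is then bounded by the inflated rate of the other outcome and approaches it.
- Eight to ten is a maximum. Smaller classes would soften the effect.
- The treatment estimate itself is not shown to be biased. The issue is its stated precision.

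**Conclusion.** The point holds conditionally. The omission is certain: one arm is delivered in groups, and neither the primary model nor the power statement allows for it. The harm depends on the class ICC. Over the assumed range it runs from negligible at 0.01 to an RMDQ power of 71–74 % and a per-outcome type I error of about 8–9 % at 0.10; it becomes material from about 0.05. Pain keeps more than 90 % power by design effect alone, so the practical weight falls on RMDQ and, to a smaller extent, the PCL-C subset.

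These figures assume 48 yoga completers spread evenly over 6 to 8 classes, the stated SDs, and no class-like correlation in the education arm. They are somewhat optimistic because the table does not charge for class-level degrees of freedom. The documents do not support a stronger statement that the planned intervals are wrong by a known amount.

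**What to change.** For pain, RMDQ and PCL-C, add to the longitudinal model a random effect for assigned yoga class. It should act on post-baseline measurements only, since the baseline survey precedes randomization, and education Veterans should be treated as singletons. Use Satterthwaite or Kenward–Roger degrees of freedom. Define class by assignment, not attendance, so that yoga Veterans who never attend stay in the intention-to-treat analysis. Restate the 97, 82 and 80 % as power under zero class correlation, followed by a range over an assumed ICC of 0.01 to 0.10.

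The cost is one variance component, the wording that goes with it, and a record of assigned class. The article says that attendance is taken but not that assigned class is recorded. Intervals become slightly wider and the stated power less favourable. A class variance estimated from about 6 to 8 classes will be imprecise, so an estimate near zero should not be read as proof of independence, and the term should not be dropped on that ground. No extra patients are needed. The article reports that the trial is still recruiting, so the change can be made before outcomes are known by arm.
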